#### Saliva samples

Participants will be asked to provide a 2 ml saliva sample. The sample, will be used to measure sncRNAs, and will be collected in SpeciMax stabilised saliva collection kits (Thermo Scientific SpeciMAX stabilised Saliva Collection Kit A50697, Life technologies Corp, Austin, Texas USA) which are pre-filled with 1 ml of virus inactivating and nucleic stabilization solution. Tubes are pre-labelled with a unique barcode linked with each participant’s unique identifier number. All samples are collected using a passive drool method. [55] Before providing each sample, participants take a small sip of water, swish the water around in their mouth and then swallow the water. This stimulates saliva release and clears any food debris that may be in the mouth. The participant’s approximate last mealtime is noted as this may influence saliva sample quality. The saliva sample is immediately stored in the freezer at − 80 °C until all samples are collected. Samples are then couriered on dry ice to laboratories in Auckland for processing and analyses.

#### Saliva sample analyses

On the day of analysis all samples will be brought to room temperature. Processing of saliva samples will involve 500 μL of each sample being aliquoted into an Eppendorf tube and centrifuged at 2,500 rpm for 5 min until all the proteins pelletise and the supernatant is clear.

#### sncRNA (miRNA) expression analysis

The sncRNA targets from saliva will be extracted using the MagMAX mirVana total RNA isolation kit (A27828, Thermo Fisher Scientific, Waltham, Massachusetts, US) using manufacturer’s instruction with modification for saliva extraction. After isolation of total RNA (including snc/miRNA), these will undergo polyadenylation, adapter ligation, reverse-transcription and miR-Amp reactions using the TaqMan™ Advanced miRNA cDNA Synthesis Kit (A28007, Thermo Fisher Scientific, Waltham, Massachusetts, US) following manufacturer’s instructions. Reactions will be performed on the standard thermocycler BioRad. The cDNA will be diluted, and real-time PCR runs for miRNA analysis will be performed using the Taqman Fast Advanced Mastermix for qPCR (4,444,964, Thermo Fisher Scientific, Waltham, Massachusetts, US) on QuantStudio™ 7 Flex Real-Time PCR System (Thermo Fisher Scientific, Waltham, Massachusetts, US).

Using TaqMan® Assays for miR-27a-5p and miR-30a-3p (assays 002445 and 000416 respectively, Thermo Fisher Scientific, Waltham, Massachusetts, US) their respective expressions will be calculated by the 2^−ΔΔCt^ method by using endogenous miRNA, one of RNU48, RNU44, U47, or RNU6B (Thermo Fisher Scientific, Waltham, Massachusetts, US) will be used as the reference genes. The ratio of miR-27a-5p/miR-30a-3p expression will be calculated. The ratio of these two miRNAs has previously been reported to differentiate concussed and non-concussed individuals; concentrations of miR-27a-5p and miR-30a-3p differentiated 75 concussed individuals from 97 non-concussed individuals with 82.4% sensitivity and 73.3% specificity. The levels of miR-27a-5p/miR-30a-3p were lower among concussed individuals and importantly showed no effect of acute or chronic exercise. These miRNAs showed similar accuracy for both sport and non-sport related concussion.

#### Surveys and questions

Survey and question data are collected and managed using REDCap (Research Electronic Data Capture) which is a secure, web-based software platform designed to support data capture for research studies. [56, 57] Participants are provided with an online link to REDCap via email. A new link is sent every seven days after initial appointment until a full return to work/study is reported. It takes approximately 10 min to complete all questions each week.

Two concussion specific questions are asked only once, seven days after the initial appointment. The first question relates to concussion history and is utilised to capture the number of previous concussions the participant has had. This information is important as prior concussion can impact recovery from subsequent concussions. [52] The second question is used to capture whether the participant’s concussion is sport related or not.

Participants are also asked to complete the Low Energy Availability in Females Questionnaire (LEAF–Q) online seven days after initial assessment and then at seven-day time intervals throughout recovery. The LEAF-Q [58] is designed and validated to evaluate physiological symptoms of insufficient energy intake or low energy availability (LEA). The LEAF-Q contains questions regarding injuries, gastrointestinal and reproductive function. In Sect. 3.2 three questions (19 items) relate to menstrual function including recent menstrual history. This questionnaire section is used to determine hormonal profile of participants and has been modified as outlined below.

Part C of Sect. 3.2 includes the following question:C: Do you have normal menstruation? Yes ☐ No (go to question C6) I don’t know (go to question C6)C1: If yes, when was your last period? 0–4 weeks ago ☐ 1–2 months ago ☐ 3–4 months ago ☐ 5 months ago or more ☐

This question has been modified to capture more accurate detail about the last menstrual cycle as follows:C: Do you have normal menstruation? Yes ☐ No (go to question C6) I don’t know (go to question C6)C1: If yes, when was your last period? 1 week ago ☐ 2 weeks ago ☐ 3 weeks ago ☐ 4 weeks ago ☐ 1–2 months ago ☐ 3–4 months ago ☐ 5 months ago or more

Participants are categorised into one of five hormone profiles as follows; 1) Follicular phase if question C1 is answered as “1 week ago”, 2) Mid-cycle if question C1 is answered “2 weeks ago”, 3) Luteal phase if question C1 is answered “3 weeks ago” or “4 weeks ago”, 4) Oligomenorrheic if C1 was answered “1–2 months ago”, “3–4 months ago” or “5 months ago or more”, 5) Using contraceptive if question 3.1a is answered “yes”.

Scoring of question 3.2 remains the same, i.e., if a participant ticks any of the boxes within the 0–4 weeks’ timeframe the same score is applied as the original question. In eumenorrheic participants this will help estimate menstrual cycle phase at point of injury. This information is used to understand any association between hormonal profile and or LEAF_Q score with symptom severity and duration of concussion.

The Brain Injury Screening Tool (BIST) is a brief screening tool for use on initial presentation after injury to guide health care pathway decision making and to monitor symptoms and recovery over time. [59] The BIST was developed in the NZ context to fit the clinical environment and to provide consistency across multiple environments and referral pathways (e.g. GP clinic, ED, Urgent Care Centres), the tool has also been psychometrically tested. There are two sections in the BIST; the first section is used to determine if there are any clinical ‘red flags’ which require referral to hospital, therefore this component is not included in this study. The second section of the BIST includes a 16-item symptom report scale for patients to rate how much they now experience the symptoms listed on a scale of 0 (not at all) to 10 (severe). Higher symptom scores are indicative of higher symptom burden. Participants are asked to complete this part of the BIST at point of presentation with injury and at seven-day time intervals throughout the study to monitor symptoms and recovery over time.

The final question asks if the participant has made a full return to work/study and how many follow-up appointments they had. The number of days between injury and full return to work/study will be used as a proxy for recovery. This question is included in the weblink sent at all timepoints (i.e., 7, 14, 21, 28 days etc.) until the participant reports they have achieved a full return to work/study, at which point participation in the study will be complete. Detail of information collected each week is included in Table 2.

**Table 2 Tab2:** Research measures and collection points

Measure	How	Who	When		
			Initial assessment	During recovery (7-day time intervals)	Full return to work/study
Saliva Samples	Passive drool into cryovial	Consulting clinician, research assistant or Lead Researcher	X		
Number of prior concussions^b^	Online^a^	Participant to complete		X	
Sport or non-sport related concussion^b^	Online^a^	Participant to complete		X	
LEAF-Q	Online^a^	Participant to complete		X	
BIST	Online^a^	Participant to complete	X	X	
Number of days from injury to recovery (full return to work/study)	Online^a^	Participant to complete			X

^a^Weblink emailed to participant

^b^Question only asked once, at first (7-day) timepoint

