## Methods/design

### Aim

The aims of this study are to: 1) determine if the time to recovery (in days) differs among groups categorised by their hormone profiles at the point of concussion injury, 2) examine whether the ratio of sncRNAs in saliva differ across groups categorised by their hormone profiles at the point of concussion injury, 3) assess whether self-reported symptoms differ among groups categorised by their hormone profiles at the point of concussion injury, and 4) investigate whether low energy availability changes across the recovery period, and if this is associated with symptoms experienced.

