## Data analysis

In this study a range of statistical tests will be used to analyse the data corresponding to the four aims. Aim 1 will use Cox proportional hazards regression to determine if the time to recovery from concussion (measured in days), differs among groups categorised by hormone profile at the point of injury (five profiles: Follicular phase, Midcycle, Luteal phase, oral contraception, IUD). Aim 2 will apply an ANOVA to compare the ratios of miR-27a-5p/miR-30a-3p expression, across these five groups. Model-estimated means and pairwise contrasts between groups will also be computed. For Aim 3, the focus is on whether self-reported symptoms, quantified both as the number of symptoms present (range 0–16) and as a total symptom burden (sum of severity scores; range 0–160), differ among hormone profile categories. These dependent variables will be analysed using ANOVA, with the five hormone profiles specified as the independent variable. Aim 4 will employ a linear mixed model to investigate changes in low energy availability across the recovery period. This model will incorporate the day of recovery and total symptom burden as fixed effects and will account for repeated measures over time by specifying participant as a random effect. The interaction between symptom burden and recovery time will also be evaluated to understand if these variables are collectively associated with low energy availability.

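### Cycle phase at injury is read from a last-period question first answered 7 to 10 days later, with no correction for the delay

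*Protocol article*

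**What the plan says.** The Aim section sets the primary aim as to "determine if the time to recovery (in days) differs among groups categorised by their hormone profiles at the point of concussion injury". The Data analysis section repeats the anchor: time to recovery is compared to see if it "differs among groups categorised by hormone profile at the point of injury". Aims 2 and 3 use the same groups.

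The profile comes from the menstrual section of the LEAF-Q: "This questionnaire section is used to determine hormonal profile of participants and has been modified as outlined below". The LEAF-Q is completed "online seven days after initial assessment and then at seven-day time intervals throughout recovery", and Table 2 has no LEAF-Q mark under initial assessment. The modified item reads "If yes, when was your last period? 1 week ago", followed by boxes for 2, 3 and 4 weeks and then longer intervals. It counts back from the day of answering and does not mention the injury.

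The classification opens with "Participants are categorised into one of five hormone profiles as follows" and then assigns *1 week ago* to follicular, *2 weeks ago* to mid-cycle, and *3* or *4 weeks ago* to luteal. Intervals of a month or more go to oligomenorrheic, and contraceptive users form their own group. The stated purpose is "In eumenorrheic participants this will help estimate menstrual cycle phase at point of injury". No adjustment for the time between injury and survey is described.

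**The concern.** The aims need the phase on the day of injury, and the rule returns the phase on the day of the survey. The boxes are about one week wide and the delay is at least one week, so this is a systematic shift rather than random noise around the right answer. A real effect of one phase could be diluted or credited to its neighbour.

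This touches the exposure of the primary aim. It also touches Aim 2, where saliva collected at initial assessment would be compared by a phase read about a week later, and Aim 3. Three of the five groups in the Data analysis section are cycle phases. In addition, a naturally cycling woman lost before the first survey has no last-period answer and so no phase, although her saliva and BIST from presentation exist.

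**Working it through.** The protocol gives no misclassification figure to reproduce. Its sample size (30, inflated to 38) does not depend on how phase is assigned.

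**Inputs from the protocol**
- Injury to presentation: 0 to 3 days (Participants and recruitment).
- Presentation to first LEAF-Q: 7 days (Surveys and questions). The gap *g* is therefore 7 to 10 days. The abstract counts the 7-day intervals from injury, which would give *g* = 7.
- Cycle length *C* for eligible naturally cycling women: 28 to 35 days (Table 1).
- The box-to-phase mapping described above.

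**Assumptions not in the protocol**
- Injury day is uniform over the cycle.
- Recall is exact, and the first survey is answered on the day it is sent and used for classification.
- Phase at injury by days since the period began, *t*: follicular 0–7, mid-cycle 7–14, luteal 14 to *C*.

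**Method.** Days since last period at the survey are *d* = *t* + *g*, less *C* if a new period has begun. Apply the mapping to *d*, compare it with the phase at *t*, and divide the mismatched days by *C*.

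**Reading A: 7-day boxes** (0–7, 7–14, then 14 onward)
- *g* = 7: all 7 follicular days are labelled mid-cycle, all 7 mid-cycle days luteal, and the last 7 luteal days follicular. Total 21 days.
- *g* = 10: 7 follicular days, 7 mid-cycle days and the last 10 luteal days are wrong. Total 24 days.

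**Reading A′: the same, but intervals beyond 28 days are answered *1–2 months ago***. For a 35-day cycle, a further 7 luteal days are labelled oligomenorrheic. Totals are 28 and 31 days.

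**Reading B: completed weeks** (*1 week ago* covers 7–14 days, and women under 7 days also tick it; *2 weeks ago* covers 14–21; 21 onward is luteal)
- *g* = 7: only women who menstruated between injury and survey are wrong, labelled follicular instead of luteal. Total 7 days.
- *g* = 10: 3 follicular days are labelled mid-cycle, 3 mid-cycle days luteal and 10 luteal days follicular. Total 16 days.

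| Reading | C = 28, g = 7 | C = 28, g = 10 | C = 35, g = 7 | C = 35, g = 10 |
|---|---|---|---|---|
| A | 21/28 = 75% | 24/28 = 86% | 21/35 = 60% | 24/35 = 69% |
| A′ | 75% | 86% | 28/35 = 80% | 31/35 = 89% |
| B | 7/28 = 25% | 16/28 = 57% | 7/35 = 20% | 16/35 = 46% |

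Rounding to the nearest week (cut-points 10.5 and 17.5 days), scored against the same phases, falls between A and B. At *g* = 7 the mismatch is 3.5 + 3.5 + 7 = 14 days (50% and 40% for the two cycle lengths). At *g* = 10 it is 6.5 + 6.5 + 10 = 23 days (82% and 66%).

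**After correction.** Using the date of the last period that began on or before the injury, the lag error is 0%. Moving each answer back one box, with the lowest box recoded as luteal, is exact under reading A at *g* = 7. At *g* = 10 with a 28-day cycle it still leaves 3 + 3 + 3 = 9 of 28 days (32%) wrong.

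**The case against.** The strongest reply concerns size. The boxes are never defined, and the item asks when the last period was, not when it began. Under completed weeks and a 7-day gap, the mapping is right for every woman who has not menstruated since injury. This stands: a reader might infer that most naturally cycling women are certainly put in the wrong phase, and the protocol does not support that as an unconditional statement. Reading A is still the more natural one, because the scoring note treats the four weekly boxes as subdividing the original 0 to 4 week box.

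The 10-day gap is the extreme and needs presentation on day 3. The abstract's anchor would fix the gap at 7. This also stands, and both ends are shown.

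The 80% and 89% figures for a 35-day cycle need the further assumption in A′. Under it, 7/35 = 20% would be mislabelled even with no delay, so part of that error is a mismatch between boxes and cycle length rather than timing.

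It is also tempting to say that anyone lost before the first survey has no profile at all. That does not hold for contraceptive users, since Table 1 screens pill and IUD use at entry.

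Finally, the wording about helping to estimate phase is hedged, and an analysis plan not shown here might add a correction. However, the article prints a direct mapping. The weekly boxes alone also do not give the earlier period date needed for women who menstruated between injury and survey. The limitations section concedes self-report and recall error, but perfect recall would leave this error unchanged.

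**Conclusion.** The inconsistency is real: the aims and analysis require phase at injury, while the collection schedule and classification rule deliver phase 7 to 10 days later. With uniform injury days, the misclassified share of naturally cycling women is 60% to 86% on the 7-day reading that the scoring note favours, and up to 89% if long intervals spill into the next box. On the completed-weeks reading it is 20% to 57%. The exact share cannot be fixed from the document. On each reading it is substantial and runs in one direction: forward in the cycle, with late-luteal women wrapping round to follicular. It is confined to the three natural-cycle groups, but those carry every phase contrast in Aims 1 to 3, so it should be corrected before any analysis.

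**What to change.** At initial assessment, where saliva and the BIST are already taken, record the calendar date of the first day of the last period. Derive cycle day as injury date minus that date, assign phase from it, and state that only this injury-date phase is used in Aims 1 to 3. State also whether the 7-day schedule runs from injury or from initial assessment, since the abstract and the Surveys and questions section differ.

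For women already enrolled (14 had started by 18 August 2023), ask for the date of the last period that began on or before the injury. Subtracting the delay from the survey answer is not enough: it gives a negative cycle day for anyone who menstruated in between.

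The cost is one extra item at initial assessment, one derivation rule and a short query to enrolled women. The sample size does not change.

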Sex differences are evident in concussion. [5–14] Females often have more severe symptoms that are longer in duration. [15–18] Studies in female athletes also show that symptom endorsement at baseline (i.e., when there is no injury) is more prevalent than that seen in males. [19] Underlying mechanisms for these observed sex differences are not yet well understood and sex as a biological variable in injury recovery remains understudied. [20] Limited data show that sex differences in concussion outcomes (i.e., severity and duration of symptoms) first appear during adolescence, are evident throughout the reproductive years, but that postmenopausal women have similar or better outcomes than men. [5] Women have a considerable physiologic change when transitioning between these life stages with altered levels of estrogen and progesterone. Bi-directional relationships between female sex hormones and concussion could influence symptoms and recovery outcomes. [4, 5, 21, 22] Primary female sex hormones, estrogen and progesterone are typically associated with reproduction, but these hormones are powerful biochemical messengers that influence every body system including, temperature regulation, macronutrient metabolism, hydration, central nervous system fatigue, and brain bioenergetics. [23–26] During reproductive years, estrogen and progesterone fluctuate across the menstrual cycle, which typically lasts 21–35 days. [27, 28] Hormone related symptoms have significant overlap with those symptoms associated with concussion and are similarly considered across physical, cognitive, emotional and sleep related domains. Low Energy Availability (LEA) occurs when dietary energy intake is insufficient to support energy expended in exercise and results in inadequate energy to support the functions required by the body to maintain optimal health; prolonged LEA is a clinical concern that disproportionately affects females, can disrupt endocrine function [29, 30] and presents with a similar set of symptoms to concussion. The prevalence of LEA ranges from 33.5% in recreationally active (tier 2 [31]) females [32] to 59% in sub-elite [33] (tier 3 [31]) and 88% in professional female football players [34] and could be a potential modifier in concussion. Female specific research is therefore needed to understand how sex hormones interact with concussion and to what extent concussion may impact hormone regulation and symptoms.

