#### Participants and recruitment

Females presenting to ED within three days of injury with suspected concussion are recruited by ED healthcare professionals. Participants are invited to participate if they are biologically female (self-report), of reproductive age (16–50 years) and have a confirmed diagnosis of concussion from the consulting healthcare professional. The diagnostic criteria for concussion are those outlined in the most recent international consensus statement from the concussion in sport group. [51] Participants will be excluded if they have Polycystic Ovarian Syndrome (PCOS), a pre-diagnosed psychiatric disorder or neurological condition (e.g. epilepsy, cerebral palsy) or if they have had more than three previously diagnosed concussions; these are known modifiers for prolonged recovery. [52, 53] These specific exclusion criteria will be ascertained by the consulting ED healthcare professional as part of the initial routine assessment for concussion. Full inclusion/exclusion criteria are shown in Table 1. The standard concussion assessment is detailed in Fig. 1. Study recruitment commenced February 2022, however there was interruption due to COVID related sickness and changes in the ED through November 2022. The study recommenced in January 2023 and is in progress.

**Table 1 Tab1:** Inclusion and exclusion criteria

Inclusion criteria	Exclusion criteria
Females of reproductive age: 16–50 years (with a menstrual cycle for a minimum of 2 years if naturally cycling)	Had three or more previously diagnosed concussions
Natural regular menstrual cycle 28–35 days long, or Currently taking Oral Contraceptive Pill (OCP), or Currently have Intra Uterine Device (IUD), or	Current concussion was more than 3 days ago
	Post-menopause
	Started taking medication that would alter reproductive hormone concentrations (Corticosteroids, e.g., Prednisone. Antidepressant or Antipsychotic medication) within the last 3 months
	Current clinical diagnosis of an eating disorder
	Pre-diagnosed psychiatric disorder
	Pre-diagnosed neurological condition
	Polycystic Ovarian Syndrome (PCOS)
	Oligomenorrheic (irregular periods), or
	Amenorrheic (loss of periods for 3 months or longer)
Confirmed diagnosis of concussion by a medical doctor (within 3 days of injury)	GCS^a^ score less than 15 at 4 h after initial assessment. These patients may be referred for a CT scan and will not be eligible for the study

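### Aim 4 measures low energy availability with a questionnaire that asks about injuries, in women who have all just been injured, and the article does not set the index concussion aside

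*Protocol article*

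**What the plan says.** Under Surveys and questions, the protocol article describes the LEAF-Q as a validated measure of the physiological signs of insufficient energy intake, and says of its content: "The LEAF-Q contains questions regarding injuries, gastrointestinal and reproductive function". It is completed "online seven days after initial assessment and then at seven-day time intervals throughout recovery". Table 2 confirms the schedule: the BIST symptom scale is collected at initial assessment, but the LEAF-Q is not. No other measure of LEA is listed.

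Table 1 requires a concussion diagnosed within three days of injury. The weekly link is sent until the woman reports a full return to work or study.

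The article sets out one modification to the LEAF-Q, finer response options for item C1 (date of last period). It says the information serves to examine "any association between hormonal profile and or LEAF_Q score with symptom severity and duration of concussion". Under Data analysis, Aim 4 is a linear mixed model for LEA with day of recovery and "total symptom burden as fixed effects", their interaction, and participant as a random effect.

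The Background notes that LEA "presents with a similar set of symptoms to concussion". The limitations section covers self-reported hormone profile, recall, return to work as a proxy, treatment not recorded, and sample size. It does not mention using the LEAF-Q just after an injury.

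**The concern.** Aim 4 asks whether LEA changes during recovery and whether it is associated with symptoms. Its outcome comes from an instrument with injury questions, its predictors are the time course and severity of an injury, and every respondent has that injury. If a woman counts her concussion when answering the injury items, the concussion sits on both sides of the model.

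The possible error is one of interpretation. An association produced by the questionnaire's content would be reported as LEA tracking concussion symptoms, and LEA as a modifier of symptoms is one of the study's stated interests. With no LEAF-Q at entry and none before injury, the data offer no earlier score against which to separate prior LEA from the effect of the index injury.

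**Working it through.** **The plan's own figure.** The article calculates a sample size for Aim 1 only, and it reproduces. Events = (1.960 + 0.842)² / (1.5² × 0.4055²) = 21.2. N = 21.2 / (0.9 × (1 − 0.2)) = 29.5, rounded up to 30; 30 / 0.8 = 37.5, rounded up to 38. It does not bear on Aim 4, for which the article states no figure.

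**How the index injury can enter the model.** Write the observed score of woman *i* at week *t* as

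Y = L + a + c_i + k·B + d·t + error,

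where L is true LEA, B is symptom burden, and the terms a, c_i, k·B and d·t are points contributed by the index injury. The Aim 4 model regresses Y on day, B and day × B with a random participant effect.

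- *a*, the same for everyone, goes into the intercept and leaves the slopes alone.
- *c_i*, fixed within a woman and unrelated to her burden, goes into the random participant effect and leaves the slopes alone.
- *k·B*, varying with severity, adds k to the symptom slope.
- *d·t*, varying with time since injury or accumulated absence, adds d to the day slope. Where it differs between women, it can also reach the symptom slope and the interaction.

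**Why the last two are possible here.** Collection continues until full return to work or study, so every LEAF-Q before a woman's last comes from someone not yet fully back. Time since injury and absence therefore run together with the model's predictors.

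**Direction.** Between women, a worse concussion could raise both the injury items and the symptom score, a positive link. Within a woman, absence accumulates while symptoms fall, a negative link. Day is also in the model. The net sign is not determined.

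**Illustration on assumed values only.** The settings were 38 women, 4 weekly scores, between-woman SD 2, residual SD 1.5, and initial burden averaging 50 (SD 20) and falling over the weeks. True LEA was unrelated to symptoms, and each setting had 150 runs. The injury items were made to add k LEAF-Q points per 50 BIST points. A second series also gave a fixed 3-point offset to a random 40% of women.

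| k | Mean slope per 50 BIST points | Runs with p < 0.05 | Mean slope with fixed offset | Runs with p < 0.05, with offset |
|---|---|---|---|---|
| 0 | −0.12 | 5% | −0.05 | 6% |
| 0.5 | 0.47 | 8% | 0.41 | 12% |
| 1 | 1.09 | 24% | 1.01 | 20% |
| 2 | 2.04 | 66% | 1.95 | 55% |

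Simulation error is √(0.05 × 0.95 / 150) = 1.8 percentage points at 5%, and √(0.66 × 0.34 / 150) = 3.9 points at 66%. The slope recovers k, as the algebra says, and the fixed offset does not bias it. The contamination is put in by assumption and with a positive sign. The table shows what a given amount would do, not that it is present.

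**The case against.** The strongest reply is that the injury items cannot be seen. The article gives no wording, recall period or points, and does not show that one acute concussion scores or that time lost is asked about. The REDCap form is not reproduced, and a condensed article may leave form wording and the exact definition of the Aim 4 outcome to the full protocol or analysis plan. The text speaks of a LEAF-Q score and does not call it a total. All of this stands, and it limits the point to a conditional one. It does not remove it: the article itself says the instrument asks about injuries, describes its modification in detail, and confines that modification to C1. Later analysis cannot recover what a woman had in mind when she counted injuries.

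A reader might also infer that contraception contaminates the score, since Table 1 admits women "Currently taking Oral Contraceptive Pill (OCP), or Currently have Intra Uterine Device (IUD), or" and the article says "Scoring of question 3.2 remains the same". The documents do not support this as a bias in Aim 4. The scoring sentence goes on to explain itself as concerning the C1 boxes within 0–4 weeks, and says nothing about how contraceptive users are scored. A stable offset in users is a between-woman shift that the random participant effect takes up. There is accordingly no case for a gastrointestinal-only score in those women, which would put two scales into one outcome.

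Nor does it follow that LEA will look too common, because no prevalence estimate or LEA cut-off is planned. The Background remark on overlapping symptoms shows why separating the two conditions matters. It is not evidence about the injury items.

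**Conclusion.** The point holds in conditional form. As the article describes it, the plan allows the index concussion to enter both the outcome and the predictors of Aim 4. If the injury items respond to it, the part that varies with severity, absence or time since injury can create or distort the LEA-symptom and LEA-time associations.

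Size and direction cannot be derived from the documents. Under the assumed settings, half a point per 50 BIST points makes little difference, while two points would yield a false association in about 55% to 66% of runs.

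It would go too far to say that the LEAF-Q score here does measure the concussion, or that the bias runs towards a positive association; neither is shown. The primary aim and its sample size are unaffected. The point is still worth acting on, because it concerns how one of the four aims is interpreted and the remedy is small.

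**What to change.** 1. Add one sentence to the injury items in REDCap asking participants not to count the head injury that brought them to the emergency department.
2. Fit the Aim 4 model twice, to the standard LEAF-Q score and to the score without the injury items, for all women including those already enrolled. The reduced score can be computed from the items already collected.
3. State in advance that an LEA-symptom association will be read as LEA only if it holds without the injury items.

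**Cost.** One line in a form that has already been adapted, and one further model fit. On 18 August 2023, 14 of 38 women had started, so at that date the wording could have reached the remaining 38 − 14 = 24 from their first LEAF-Q. The reduced score departs from the validated instrument, which is why the standard score is still reported. The standard score will also mean something slightly different before and after the wording change, whereas the reduced score is comparable across the whole cohort.
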